### A. Specific Aims

We propose to conduct two intervention trials using multiple vitamin-mineral supplements to evaluate the relation between such supplements and esophageal cancer mortality. One trial will be conducted in patients diagnosed with esophageal dysplasia and the other in the general population. We plan, in addition, to evaluate the effect of these supplements on regression/progression of dysplasia, esophageal and total cancer incidence, total cancer mortality, and total mortality.

To test the hypothesis that esophageal cancer mortality is related to nutrient intake, we will provide daily vitamin-mineral supplements to individuals and follow them for 5 years for the development of cancer in a randomized, doubled-blind, controlled intervention. These two studies will be conducted in Linxian (Henan Province) in the People's Republic of China (PRC). Linxian, a rural county with population 800,000, was selected because it has the highest rate of esophageal cancer in the world, and because there is suspicion that the population's chronic deficiencies of multiple nutrients may be etiologically involved.

Based on prevailing rates, over 1000 esophageal cancer deaths are expected in the populations to be studied. Over the 5-year study period, there will be greater than 90% power to detect a 40% reduction in esophageal cancer mortality among treated dysplasia patients, and similar power to detect a 20% reduction in the treatment group from the general population. The finding of substantially lower esophageal cancer mortality rates in the treated groups would provide strong evidence that minerals and/or vitamins are protective against cancer in humans.

### B. Significance of the Proposed Research

The highest worldwide incidence and mortality for cancer of the esophagus occurs in the People's Republic of China. A nationwide survey of mortality conducted there in 1973-75 identified esophageal cancer as the second leading cause of cancer death, accounting for 27% of all cancer deaths in men and 20% in women.(1) The survey showed distinctive geographic variation within the country, with a 670-fold gradient between counties with the highest and lowest age-adjusted rates. Although elevated mortality is seen in several parts of the country, the most prominent cluster forms in north-central China, particularly in the Taiheng mountain area on the border of Henan, Hebei, and Shansi Provinces. Within this area in Henan Province is Linxian, a county with a population of 800,000 where the crude rates per 100,000 were 136 in males and 104 in females during 1977-82, and where the cumulative death rates to age 75 for esophageal cancer exceed 20% in both sexes.(2) Although there are only limited historical data, it appears as if esophageal cancer has long been a problem in these areas and that there has been little change in the death rates from 1959-82.

Abnormalities thought to represent esophageal cancer precursor lesions are common in Linxian. Past cytologic and endoscopic surveys in Linxian indicate that only about 20% of the adult population have "normal" esophageal epithelial. (3) The remaining 80% have some degree of esophagitis, including approximately 20% with esophageal dysplasia.

### Previous Studies of Esophageal Cancer in China

Numerous epidemiologic and laboratory investigations have been conducted in areas of China at high and low risk of esophageal cancer.(3-10) We have twice organized multidisciplinary surveys to assess levels of environmental factors (e.g., trace elements in water, food, sera, urine, and hair; nitrates in well water; consumption of pickled vegetables, moldy breads, and other foods; nutrient levels in blood) for brigades, communes, or counties in relation to the esophageal cancer rates for these geographic units.(4-6) Case-control interview studies have been conducted in Xinjiang and Jiangsu Provinces.(4) The most intense analytical study, however, has been in Linxian, where the characteristics of esophageal cancer and its precursor lesions have been under study for the past 25 years.

The studies have provided a series of clues to etiology, but have not yet conclusively pinpointed a specific carcinogen responsible for the elevated esophageal cancer rates. They have identified significant differences, noting that the high-risk areas tend to be rural and poor, with dry climates, infertile soils, and water often in short supply.(4) Diets have been typically low in fruits and vegetables. There appear to be widespread deficiencies of multiple nutrients (riboflavin in particular, but also vitamins A and C, zinc, molybdenum and others).(3,7) The previous studies suggest that specific foods commonly eaten in Linxian and other areas may contribute to the initiation of the tumors. Under suspicion are pickled vegetables and other foods that also become fermented or moldy; including moldy breads and cheeses in Xinjiang.(4-6) Silica fragments, most likely from ingested millet, have been found in esophageal tissue from cancer patients.(8) Nitrosamines have been detected in several of these foods in high-risk areas, and Ames tests have revealed evidence of mutagenicity in samples of the pickled vegetables.(4,9,10) One small experimental study conducted in China also showed that cancers of the esophagus and forestomach developed in rats fed moldy cornbread, while another showed that fungal contamination could promote the synthesis of nitrosamines.(9) Esophageal fungal infections were diagnosed in the majority of patients with esophageal cancer in one survey in Linxian.(4) The previous studies indicate that smoking and drinking -- the major determinants of esophageal cancer in Western societies -- may play some role in China, but relatively minor ones. Familial clustering has also been observed, but it seems likely that the high cancer rates are predominantly of environmental origin.

We are currently conducting a case-control study on esophageal cancer in Linxian in collaboration with NCI. This study (supported by contract number N-CP2-1012) will

more fully evaluate the etiologic role of multiple risk factors, such as moldy or fermented foods, smoking and drinking, family history of cancer, exposure to nitrosamines, and other factors. The case-control study will also obtain dietary histories and attempt to assess micronutrient status in cases compared to controls. However, the role of micronutrients status can best be evaluated via a prospective experimental trial. Thus, we are pleased to respond to NCI's request to conduct an intervention trial to test the hypothesis that vitamin/mineral deficiency is related to the high risk of esophageal cancer in Linxian.

As noted, the reasons for the exceptional risk of esophageal cancer in certain areas of north China are not yet known, but they may be related to increased exposure to specific carcinogens among a population unusually susceptible because of chronic nutritional deficiencies. Consistent evidence is now emerging from a number of epidemiologic investigations conducted outside China that patients with epithelial cancers, including those of the esophagus, often had diets characterized by reduced intakes of certain foods, particularly fruits and vegetables. Epidemiologic studies conducted in the United States(11-13), Puerto Rico(14), Japan(15), Iran(16), and South Africa(17), all have shown relatively strong associations between esophageal cancer risk and poor nutrition. Laboratory evidence suggests that specific nutrient deficiencies may be responsible for these associations. Low levels of vitamin A are suspect since retinoids have marked anti-promotion properties in experimental studies.(18) An independent influence of pro-vitamin A (beta-carotene) has also been postulated on biologic grounds.(19) Riboflavin deficiency can produce esophageal epithelial changes and affect carcinogen metabolism, and enhance carcinogenesis (20-21), while vitamin C is thought to block the formation of nitrosamines (22), and vitamin E to act as an antioxidant and inhibitor of chemical carcinogenesis (23). Mineral deficiencies also can modify cancer incidence. Zinc deficiency has been shown to enhance methylbenzyl-nitrosamine-induced esophageal carcinogenesis in rats.(24) Zinc also influences the release of vitamin A from liver stored in humans, with serum concentrations of retinol tending to be low in persons with low levels.(25) Studies in our laboratories have shown that molybdenum can inhibit cancers of the forestomach in rats.(26)

In summary, the strong weight of evidence from these experiments suggests that several vitamins and minerals can have a pronounced effect on tumor development. Combined with the results of the epidemiologic investigations, an hypothesis emerges that low intake (although not necessarily low enough to induce frank clinical deficiencies) of nutrients can enhance risk. Thus vitamin and mineral supplementation among persons with low levels of consumption of several nutrients and with high rates of cancer may result in a reduction in cancer risk.

### C. Pilot Intervention Study

The CICAMS has been concerned with the problem of esophageal cancer in Linxian since 1959, when a field station was established there to improve diagnosis, treatment, and public health work aimed at the prevention of esophageal cancer. In conjunction with the Linxian Esophageal Cancer Research Institute and the Henan

Province Cancer Institute, the CICAMS has maintained for several years an active, reliable surveillance system and registry of esophageal cancer in Linxian. Our long commitment to Linxian has earned the trust and cooperation of local institutions.

The nutritional intervention trials proposed herein will build directly on the experience of a pilot study begun in October 1982, under an NCI contract (N-CP2-1012) between the CI, CAMS, and the U.S. NCI.

Pilot studies were undertaken to assess the feasibility of large scale interventions. The specific questions the pilot studies were designed to answer included:

- (1) Can sufficient numbers of persons form the general population be recruited?
- (2) Can sufficient numbers of dysplasia patients be identified and recruited?
- (3) How compliant will participants be?
- (4) Can the administrative logistics of patient recruitment, information collection, pill delivery, and follow-up be managed?
- (5) What is the current nutritional status of the population?
- (6) Will supplementation with U.S. Recommended Daily Allowance (RDA) levels of vitamins improve low or deficient states?

Two pilot trials were conducted, the first involving the general population and the second involving persons diagnosed with severe esophageal dysplasia.

For the general population pilot, 21 production teams (villages) were randomly selected from two communes (Yaocun and Rencun) in northern Linxian. A central census roster listed 937 names of persons aged 40-69. Sixty-two (7%) proved to be ineligible for the following reasons:

- suffering from esophageal cancer - 7

- suffering from other cancers - 2
- suffering from other debilitating disease - 5
- had already died - 18
- temporarily assigned work outside the county - 16
- other (incorrect age, erroneous or duplicate listing, etc.) - 14

852 of the 875 eligible subjects (97%) agreed to enroll in the general population pilot trial. For the dysplasia pilot trial, 91 persons from Yaocun and Rencun communes most recently discovered by balloon-swallow cytology examination to have severe dysplasia were recruited. All 91 agreed to participate. Criteria for the diagnosis of dysplasia are given in Appendix 1. All participants in the pilot studies were given One-A-Day (Miles Laboratory) multiple vitamin tablets for 6 months.

Barefoot doctors visited the subjects during the trial to distribute pill packs. Table 1 shows the losses to follow-up during the course of the trial. Losses were generally due to death, cancer, or other debilitating diseases occurring among participants, or to movement away from the study area. At the end of the 6-month trial, losses were about 3%.

Table 2 gives the percent of enrolled participants who refused to take any of the distributed pills. At the end of the study period, these refusal rates were 2.5%. Among those taking at least some pills, over 95% (as judged by counting unused pills) were taking the large majority of the pills by the end of the trial (Table 3). In addition to counting unused pills, compliance were administered loading-dose tests for urinary riboflavin prior to pill-taking and at either 3, 5, or 9 weeks after the start of supplementation. Analysis of the previous data is still ongoing, but Table 4 shows that average levels of riboflavin were markedly higher after than before supplementation.

**Table 1.** Cumulative Percent Lost to Follow-up

During the 6-Month Pilot Intervention Trial

| Month | Percent |
|--------------|----------------|
| 1            | 1.6            |
| 2            | 1.7            |
| 3            | 1.7            |
| 4            | 3.1            |
| 5            | 3.1            |
| 6            | 3.3            |

**Table 2.** Cumulative Percent of Participants Refusing

to Take any Pills During the 6-Month Pilot Intervention Trial

| Month | Percent |
|--------------|----------------|
| 1            | 0.0            |
| 2            | 2.4            |
| 3            | 2.4            |
| 4            | 2.4            |
| 5            | 2.5            |
| 6            | 2.5            |

Table 3. Monthly Percent of Participants Taking  
at Least 80% of the 6-Month Pilot Intervention Trial

| Month | Percent |
|--------------|----------------|
| 1            | 92.3           |
| 2            | 88.6           |
| 3            | 93.9           |
| 4            | 97.6           |
| 5            | 96.8           |
| 6            | 96.1           |

Table 4. Mean Riboflavin in 4-Hour Urine Samples  
Before and During the Pilot Intervention Trial

| Time of Specimen | n | x (mg) |
|-------------------------|----------|---------------|
| Collection       |          |               |
| Before                  | 116      | 756           |
| After 3 weeks           | 40       | 1362          |
| After 5 weeks           | 44       | 1423          |
| After 9 weeks           | 32       | 1368          |

Nutritional assessments involving laboratory assays of blood and urine were conducted prior to the start of and 4 months after supplementation. The assessments were carried out on 100 randomly selected individuals taking daily pills and (as a control) on 51 similarly-aged individuals from commune production teams not participating in the pilot study. High-pressure liquid chromatography (HPLC) analyses of serum for retinol, beta-carotene, and tocopherol have been conducted, and red blood cells have been assayed for glutathione reductase activity (as a more sensitive measure of riboflavin status than provided by the urine tests). Plasma and urinary ascorbic acid and urinary niacin and thiamine are also being determined. Results are not yet fully available, but preliminary data from the HPLC analysis (conducted at the New Jersey

Medical School in the laboratory of Professor [name]) show sizeable shifts toward increasing status for retinol and vitamin E (both included in the One-A-Day pills), but not beta-carotene (not included in the pills).

The pilot study thus suggests that a vitamin intervention trial will be well accepted in Linxian. Indeed compliance, as judged by the pill counts, was exceptionally high. Of course, the disappearance of a pill from the pill pack does not guarantee that the pill was actually taken by the participant, but our initial laboratory analyses provide biochemical confirmation from both urine tests (reflecting recent pill taking) and blood tests (reflecting longer-term pill taking) that compliance was high. The pilot study also led to the establishment of an organizational system which can be readily expanded to accommodate a larger trial.

In summary, progress to date indicates that a population-based nutritional intervention study of esophageal cancer in Linxian is feasible. Pilot Study results have clearly shown that: patients can be identified and recruited; compliance is excellent; administrative logistics can be handled; nutritional deficiencies are numerous; and low dose vitamin supplementation improves nutritional status.

#### D. Experimental Design - Intervention Plan

##### 1. Participant Selection

###### Inclusion Criteria (both interventions):

- a. Limited to 3 northern communes (Yaocun, Rencun, and Donggang).
- b. Males and females aged 40-69.
- c. Able and agree to participate for duration of trial.

In addition, for the dysplasia trial only, persons must have been found to have severe (group 1 or 2) dysplasia in a mass balloon cytology screening conducted in the fall of 1983.

###### Exclusion Criteria.

- a. Currently taking vitamins regularly.

- b. Malignancy or other debilitating disease.
- c. Taking certain specific medications (e.g. the traditional drug, Anti-Tumor B3 or synthetic retinoids).

## 2. Pre-Study Requirements

- a. Complete a pre-study evaluation which includes having a physical examination and filling out a short questionnaire asking about demographic information and esophageal cancer risk factors (see Appendix 2).
- b. Give informed consent.

## 3. Intervention Assignment

### Dysplasia Component

Participants will be recruited from among residents of Yaocun, Rencun and Donggang communes identified as having severe esophageal dysplasia in the December 1983, balloon-swallow cytology screening. The identification and interviewing of dysplasia patients is expected to take one month. All eligible dysplasia subjects who complete the pre-study requirements will be randomized by individual in blocks of 8 into treatment (or placebo) groups, stratified by age (5-year groups), sex, and commune. Actual enrollment of subjects for the dysplasia trial is expected to take an additional 2 months to complete.

### General Population Component

Participants will be recruited from census lists of eligible residents aged 40-69 from three communes (Yaocun, Rencun, and Donggang) in northern Linxian (excluding those already taking part in the dysplasia component). Census figures indicate that the current population of the 3 target communes for males and females age 40-69 is 33,643.

The pre-study evaluation for these subjects is expected to take 2-3 months and will be started after the dysplasia trial accrual is complete. Those eligible and completing pre-study requirements will be randomized by individual in blocks of 8 into treatment (or placebo) groups, stratified by age (5 year groups), sex, and commune. Accrual for the general population trial is expected to take 4 months to complete.

For both the dysplasia and the general population components, randomization will be conducted in Beijing and the key will be kept at NCI so as to keep the trial double blind for all involved persons in Linxian and Beijing.

#### 4. Intervention Plan

The type and dosage of vitamins and minerals to be administered will differ for the two trials. For both trials, participants will receive various combinations of vitamin A, beta-carotene, riboflavin, niacin, vitamin C, vitamin E, selenium, zinc, and molybdenum, in doses between one and three times the U.S. Recommended Daily Allowances (RDA). The RDA for the nutrients with National Academy of Sciences-specified levels are:(27)

vitamin A - 5000 I.U., riboflavin - 1.6 mg, niacin - 18 mg,

vitamin C - 60 mg, vitamin E - 10 mg, and zinc - 15 mg.

Different study designs will be used for the two trials. The dysplasia trial will use a simple two-group design with one-half the patients assigned to receive multivitamin-multimineral pills to be taken daily. The other one-half participants will receive placebos identical in appearance to the active pills (see Table 5 for exact dosages).

For the general population trial, a factorial design will be used. The form of design to be used is a one-half replicate of a 2X4 factorial design.

The 4 proposed factors include:

A - vitamin A, beta-carotene, zinc

B - riboflavin, niacin

C - vitamin C, molybdenum

D - selenium, vitamin E

A full 4-factor factorial design would include  $2 \times 4 = 16$  different treatment groups (shown below).

|                |           |           |             |
|----------------|-----------|-----------|-------------|
| Placebo | A         | B         | AB   |
| C              | AC | BC | ABC         |
| D              | AD | BD | ABD         |
| CD      | ACD       | BCD       | ABCD |

One-half repetition includes only 8 treatment groups (the 8 underlined above).

This design was chosen because it will allow us to separate the main effects of various grouped factors (and certain of the interactions between factors) without requiring the excessive number of treatment groups needed for a 24 full factorial design or a factorial design evaluating greater numbers of factors. Further discussion of the rationale behind this choice of design is given in Appendix 3.

All treatment groups (including placebo) will have a small amount of thiamine (0.375 mg or 25% RDA) included. The addition of thiamin allows us to provide a small amount of a vitamin potentially useful for general health status, but which by itself would be unlikely to influence esophageal cancer incidence or mortality.

It is anticipated that the pills for both trials will be formulated in the United States and packaged in pill packs in China.

The barefoot doctors will deliver the vitamin pills in packs containing a 4-week (28-day) supply. At the end of each 28-day period, the barefoot doctor will collect the used pill pack and give out a new pack. Each will be labelled with the subjects study number and name.

Before starting the trials, a manual of field operations for interviewers, pill distributors, and other field staff will be developed and training sessions will be held to assure that standardized procedures are adhered to in all study procedures, including interviewing, distribution of pills, monitoring of compliance, and documentation activities.

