#### (c.) Data Analysis

The methods of analysis to be applied to the data collected during these trials include simple contingency table analysis and Cox's method of regression analysis for survival data.(34) The use of regression methods will allow for incorporation of variables stratified on at randomization and adjustment for risk factors which are found by the initial interview to be nonrandomly distributed between treatment groups.

Analysis of the dysplasia trial data will allow us to make a statement about the effect of the combined multivitamin-multimineral preparation only, while in the general population trial we will be able to separate out the effects of the several factors.

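### The half-replicate in section D.4 cannot separate any two-factor interaction from its complementary pair, although the protocol says that some interactions can be separated

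*Protocol*

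**What the plan says.** Section D.4 (Intervention Plan) sets the design of the general population trial: "The form of design to be used is a one-half replicate of a 2X4 factorial design". The printed 2X4 stands for two to the fourth power, as the sixteen cells in the table show; the lost exponent is a matter of text extraction and is not at issue here.

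The four factors are "A - vitamin A, beta-carotene, zinc", "B - riboflavin, niacin", "C - vitamin C, molybdenum" and "D - selenium, vitamin E". The fraction is fixed cell by cell: "One-half repetition includes only 8 treatment groups (the 8 underlined above"). The underlined cells are placebo, AB, AC, BC, AD, BD, CD and ABCD.

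The reason given for the choice is that "it will allow us to separate the main effects of various grouped factors (and certain of the interactions between factors"). D.4 does not say which interactions are meant, lists no aliases, and names no interaction as assumed nil. It refers the reader to Appendix 3 for more on the rationale. In the document at hand, Appendix 3 is only a pointer to a tab of study publications.

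**The concern.** In a half-replicate, every effect shares its contrast with one other effect. Which effects are paired depends on the cells chosen. The phrase in D.4 would be reasonable for some half-replicates. With I = ABC, for example, A×D, B×D and C×D would each be free of other two-factor interactions, at the price of aliasing A, B and C with two-factor interactions. The fraction in D.4 makes the opposite trade. It protects the main effects and leaves no interaction separable.

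The risk is one of attribution. An analyst who relies on D.4 could add an A×B term to a Cox model. The model would fit without warning, and the result would be credited to vitamin A, beta-carotene and zinc acting together with riboflavin and niacin. The same coefficient could equally arise from vitamin C and molybdenum acting together with selenium and vitamin E. A larger sample cannot resolve this, because the two contrasts compare the same groups of people.

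**Working it through.** **Inputs.** The eight underlined cells and the four factors, from Protocol D.4. For the power check: 28,000 participants, P0 = 0.029, P1 = 0.0232, 14,000 per arm and one-sided alpha 0.05, from D.9(a) and D.9(b).

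**Step 1: the plan's own count.** Four two-level factors give 2^4 = 16 cells, and half of them is 8. Eight are underlined, so the stated number is reproduced. Each factor is given in 4 of the 8 groups.

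**Step 2: signs.** Code each factor + if given and − if not. An interaction column is the product of its factor columns.

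| Group | A | B | C | D | AB | CD | AC | BD | AD | BC |
|---|---|---|---|---|---|---|---|---|---|---|
| Placebo | − | − | − | − | + | + | + | + | + | + |
| AB | + | + | − | − | + | + | − | − | − | − |
| AC | + | − | + | − | − | − | + | + | − | − |
| BC | − | + | + | − | − | − | − | − | + | + |
| AD | + | − | − | + | − | − | − | − | + | + |
| BD | − | + | − | + | − | − | + | + | − | − |
| CD | − | − | + | + | + | + | − | − | − | − |
| ABCD | + | + | + | + | + | + | + | + | + | + |

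The AB and CD columns are identical, as are AC and BD, and AD and BC.

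**Step 3: defining relation.** Every cell contains 0, 2 or 4 factors, so the product ABCD is + in every row, that is, I = ABCD. Multiplying both sides by each effect gives:

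- two-factor interactions: AB = CD, AC = BD, AD = BC
- main effects: A = BCD, B = ACD, C = ABD, D = ABC
- the four-factor interaction is aliased with the overall mean.

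**Step 4: what the A×B contrast estimates.** Write y for the group outcome on the analysis scale. The contrast is

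[y(placebo) + y(AB) + y(CD) + y(ABCD)]/4 − [y(AC) + y(BC) + y(AD) + y(BD)]/4.

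The C×D contrast is the same expression. Its expectation is the sum of the A×B and C×D effects.

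**Step 5: rank.** A model with the mean, 4 main effects and 6 two-factor interactions has 1 + 4 + 6 = 11 terms, but the matrix over the eight groups has rank 8. The shortfall of 3 is one for each alias pair.

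| Quantity | Estimable from the eight groups |
|---|---|
| Main effects (averaged over the other factors) | 4 of 4, if three-factor interactions are nil |
| Individual two-factor interactions | 0 of 6 |
| Pair sums AB+CD, AC+BD, AD+BC | 3 of 3, with no condition on individual two-factor terms |

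A model with only AB, AC and AD added to the main effects has 8 terms and rank 8. Those three coefficients can then be estimated, but only because CD, BD and BC have been set to zero.

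**Step 6: effect on power.** Each main effect compares four groups with four. With 28,000/8 = 3,500 per group, that is 14,000 against 14,000, the split used in D.9(b). The pooled two-proportion formula is

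Power = Φ{[|P0 − P1|√n − z√(2p̄(1 − p̄))] / √[P0(1 − P0) + P1(1 − P1)]}, with p̄ = (0.029 + 0.0232)/2 = 0.0261 and z = 1.645.

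- |P0 − P1|√n = 0.0058 × 118.32 = 0.6863
- z√(2p̄(1 − p̄)) = 1.645 × 0.2255 = 0.3709
- denominator = 0.2254
- Φ[(0.6863 − 0.3709)/0.2254] = Φ(1.40) = 91.9%, against 92% stated.

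The aliasing of interactions does not enter this calculation.

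**The case against.** The strongest defence is that D.4 makes a hedged claim. It says that some interactions can be separated, not all, and fractional designs are ordinarily read with some effects assumed nil. If one member of each pair is assumed absent, three interactions can be estimated, as Step 5 confirms. That much stands. But separation then comes from the assumption, not from the design, and the sentence offers it as a property of the design. The assumption is not in the text at hand. Appendix 3 might contain it, so its absence from the whole plan cannot be asserted. Nothing in Appendix 3 could change which columns of the sign table coincide.

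A second defence is that no interaction test is planned. D.9(c) names contingency tables and Cox regression, and D.9(b) discusses power for each factor only. That also stands. The misattribution described above is a risk that the wording invites, not an analysis that the protocol specifies.

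Three stronger readings are tempting, and the document does not support them.

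- A reader might infer that the trial cannot separate its four factors, because each main effect has a three-factor alias. That is true of any resolution IV design. All four main effects are clear of every two-factor interaction, and three-factor interactions are commonly taken as negligible.
- A reader might infer that D.9(c) repeats the error where it says that "in the general population trial we will be able to separate out the effects of the several factors". That sentence contrasts this trial with the dysplasia trial, which tests one combined preparation. It does not mention interactions, and it holds for main effects under the usual assumption.
- A reader might count the lack of any single-factor group as a defect. Such a group is indeed absent, and the effect of one factor alone against placebo cannot be recovered once two-factor interactions are allowed. But the protocol promises no such comparison.

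**Conclusion.** The statement about interactions in D.4 is wrong as written. For the eight cells listed, 0 of 6 two-factor interactions can be separated, and three pair sums are all that the data can supply on two-factor interactions. This is exact algebra and depends on no assumption about event rates or sample size. It rests only on the underlining as printed, which marks exactly eight cells and forms a regular half-replicate.

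The conclusion goes no further than that. The four main-effect comparisons stand if three-factor interactions are negligible, and the stated power is unchanged. Severity is minor to moderate: the claim forms part of the stated reason for the design and could lead to an interaction being credited to the wrong pair of nutrient groups, but no planned comparison depends on it.

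**What to change.** In D.4, replace the parenthesis about interactions with three statements:

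1. The fraction has defining relation I = ABCD, so AB is aliased with CD, AC with BD, and AD with BC.
2. Main effects are interpreted on the assumption that three-factor interactions are negligible.
3. Interactions will be assessed and reported only as the three pooled contrasts AB+CD, AC+BD and AD+BC, and no single two-factor interaction will be claimed by name.

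D.9(c) needs no change.

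The cost is a few lines of protocol text and the reporting of three contrasts. Treatment groups, randomisation, sample size, endpoints and power stay as they are. What is given up is a claim that the chosen cells cannot support.
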